### Selecting Change

Two major changes will be implemented. Implementation of a risk-based protocol for VTE prophylaxis for all Department of Neurosurgery patients undergoing elective surgery, and training of direct patient care staff on the protocol across the Departments of Neurosurgery and Neuro Critical Care (NCC). The following steps outline the QI protocol:

For all patients admitted to the Neurosurgery or NCC service and undergoing a neurological surgery, use mPpx with SCD intraoperatively and until discharge. An exception is patients in whom mPpx with SCD is contraindicated, such as patients with known DVT or lower extremity injury.For patients with intracranial hemorrhage, we will obtain stability imaging at 24-48 hours before starting cPpx.For all patients admitted to the Neurosurgery or NCC service and undergoing an elective neurological surgery, provide cPpx starting at 24 hours until discharge, unless an absolute contraindication to anticoagulation is present (per #5).Check creatinine clearance (CrCl) and choose cPpx with either enoxaparin if CrCl is >30 mL/minutes or UFH if CrCl≤30 mL/minutes. Dosing for all patients is according to weight and BMI, as obesity is an independent risk factor for hypercoagulability. Small studies have shown an advantage of weight-based dosing in achieving target anti-Xa levels with enoxaparin administration [32,33]. A clinical trial has also demonstrated a reduction in VTE rates for patients on UFH cPpx when using both BMI and weight (weight>100 kg and BMI≥40 kg/m^2^) [20]. For weight-based enoxaparin prophylaxis, the standard dose is 40 mg subcutaneously daily. For patients weighing less than 50 kg, the dose is 30 mg subcutaneously daily. Patients with a BMI more than 40 kg/m² should receive 40 mg subcutaneously twice daily, and those with a BMI more than 50 kg/m² should receive 60 mg subcutaneously twice daily. For weight-based unfractionated heparin prophylaxis, the standard dose is 5000 units subcutaneously every 8 hours. Patients with a BMI more than 40 kg/m² and a weight over 100 kg should receive 7500 units subcutaneously every 8 hours.Per AAST VTE prophylaxis in the ICU (2021) [7], an absolute contraindication to cPpx for patients hospitalized with trauma is active hemorrhage or recent spine or intracranial surgery. This is in addition to absolute contraindications to therapeutic anticoagulation, including a prior complication while on anticoagulation therapy or recurrent VTE while on an adequate dose of cPpx, or ongoing risk due to life-threatening bleeding. Risk of life-threatening bleeding includes long-bone fractures, severe pelvic fractures, plus a long-bone fracture, TBI, SCI, and medical conditions predisposing to bleeding. Patients who meet these criteria will be assessed with a stability scan before inclusion in this protocol. Relative contraindications to cPpx include epidural hematoma, risk of wound complications, and neurologic decline. Patients with relative contraindications will be included in the protocol.VTE therapy will be continued until the patient is discharged from the hospital and no longer immobilized.Training on this protocol was provided to all health care providers involved in postoperative neurosurgery patient care. A flowchart is displayed in common work areas (Figure 1). This training took place between Inservice in September and October 2023.

Continuous improvement is built with small incremental changes, using a systematic scientific approach to test their impact and feasibility. The Plan-Do-Study-Act cycle will be used as a model on which to structure tests of change. This includes continuous analysis of errors and successes of the protocol and subsequent protocol adaptation for the duration of the project. Dynamic data will be assessed through a run chart with data points added monthly, but with interim analysis every 3 months. Interim analyses will be discussed before changing the protocol for such quality improvement adaptations. A formal statistical analysis will be performed with a *t* test comparing NSQIP and postprotocol end-of-study VTE rates at both 12 and 24 months post implementation. Stratification based on malignancy and cranial versus spine procedures will also be assessed, as will be the confounding process and balancing measures.

Missing data will be handled through checking at each interim review. Any record missing critical outcome or key covariate information will be excluded from regression analyses. In addition, we will conduct sensitivity analyses to assess the impact of any missing data on VTE rates. Discrepancies will be resolved by consensus and reported, if indicated. Interim analyses with department reports will be performed every 3 months, but every VTE event will trigger an analysis of the variables described in this protocol. Analyses will consider barriers to change and adequacy of the protocol to guide protocol modifications and continuous implementation of improvements.

Additional guidance has been incorporated to inform future iterations of the protocol, including considerations for patients with comorbid atrial fibrillation or those already on antiplatelet therapy [34]. Implemented changes will be made based on recent evidence in the literature [35].

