## Discussion

### Expected Findings

Our review of the literature (summarized in Multimedia Appendix 1) demonstrated that all published guidelines by non-neurosurgical societies are largely inconsistent. While some suggest against the use of pharmacological prophylaxis in the majority of patients undergoing neurosurgery, others suggest stratifying patients based on risk of VTE, including those with malignancy or immobilization, and providing pharmacological prophylaxis in the high-risk group. Moreover, the choice of anticoagulant is different between published guidelines, and most do not consider weight-based dosing.

In devising our protocol, we borrowed heavily from the trauma and neurocritical care literature when choosing the timing, agents, and dosing for VTE cPpx. NASS working group on VTE prophylaxis [9] notes that the safety and utility of cPpx is controversial, and the literature does not support a specific perioperative start time point nor duration of cPpx. However, the working group acknowledges that LMWH initiated on the day of surgery may be safe for patients undergoing elective spine surgery and makes a consensus-based recommendation for it in their 2009 guidelines [9]. On the other hand, the ACCP recommends initiating cPpx in trauma neurosurgical patients within 24-72 hours of admission pending a stability scan [7]. The NCC guidelines [36] alternatively note that VTE cPpx should be initiated after 24 hours of admission for patients with aneurysmal subarachnoid hemorrhage, after 48 hours for patients with intracerebral hemorrhage, and within 24-72 hours for patients with TBI, but not before. We have elected to initiate cPpx for all admitted patients on the neurosurgery service within 24-48 hours of scheduled surgery. Patients who have a contraindication to anticoagulation or are at a high risk of intracranial bleeding will enter the protocol pending a stable head computed tomography.

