It is important to consider that a subset of patients may already be on a therapeutic dose of anticoagulation or antiplatelet medications for a history of DVT or PE before hospitalization. Such medications are typically held the evening before a neurosurgical procedure, or in cases of emergency surgery, may be reversed on an individual patient basis. Postoperatively therapeutic dose of anticoagulation or antiplatelet medication may be restarted in these patients. Such patients also continue their regular dose upon discharge. We do not provide a prescription for mechanical VTE prophylaxis other than early mobilization with physical therapy.

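### Steps 3 and 5 of the prophylaxis protocol conflict for absolute contraindications that a stability scan cannot clear, so heparin or enoxaparin could be started on a test that does not bear on the contraindication

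*Protocol article*

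**What the plan says.** The steps in Selecting Change run together in the text. Counted in order they are: compression devices (1), imaging for intracranial hemorrhage (2), cPpx for elective surgery (3), choice and dose of agent (4), contraindications (5), duration (6) and training (7). The cross-reference in step 3 confirms this numbering.

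- **Step 3**, for elective patients: "provide cPpx starting at 24 hours until discharge, unless an absolute contraindication to anticoagulation is present (per #5").
- **Step 5** lists the absolute contraindications. For trauma patients these are active bleeding and a recent operation on the spine or brain. It adds contraindications to therapeutic anticoagulation: "a prior complication while on anticoagulation therapy or recurrent VTE while on an adequate dose of cPpx", and a continuing risk of life-threatening bleeding. The examples of that last risk are certain fractures, TBI, SCI and medical conditions that promote bleeding.
- **Step 5**, next sentence: "Patients who meet these criteria will be assessed with a stability scan before inclusion in this protocol". Relative contraindications follow: "Patients with relative contraindications will be included in the protocol".
- **Discussion, Expected Findings**, on which groups come in by way of a scan: "contraindication to anticoagulation or are at a high risk of intracranial bleeding will enter the protocol pending a stable head computed tomography".
- **Step 6**, on duration: "VTE therapy will be continued until the patient is discharged from the hospital and no longer immobilized".

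**The concern.** Step 3 is an instruction to withhold. Step 5 names the conditions that trigger it, but the only consequence it attaches to them is a scan followed by inclusion. No listed condition ends in exclusion. A scan can show whether a bleed is stable. It cannot show whether a past anticoagulant complication would recur, whether prophylaxis that failed before would fail again, or whether a patient has a bleeding disorder.

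The project exists to replace varied practice with a single rule. Here one clinician can withhold under step 3 and another can scan and start under step 5, each with a claim to compliance. The matter touches safety: Ethical Considerations says the project adds no risk beyond standard care, and Outcomes commits to monitoring bleeding events and variation in adherence. Such patients are also expected, because Outcomes names a history of VTE despite prophylaxis among its balancing measures.

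**Working it through.** The plan states no figure on this point, so the check sets the rules side by side.

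**Contraindications**

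| Category in step 5 | Step 3 | Step 5 and Discussion | Can imaging settle it? | Do the rules fit together? |
|---|---|---|---|---|
| Active bleeding (trauma) | withhold | scan, then include | yes | yes: hold, scan, start |
| Recent spine or brain surgery (trauma) | withhold | scan, then include | yes, for bleeding at the site | yes |
| Life-threatening bleeding risk from TBI or SCI | withhold | scan, then include | yes, if the scan covers the injured site | yes |
| Life-threatening bleeding risk from a medical condition | withhold | scan, then include | no | **no** |
| Earlier complication on anticoagulants | withhold | scan, then include (broad reading) | no | **no** |
| Recurrent VTE despite adequate prophylaxis | withhold | scan, then include (broad reading) | no | **no** |

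Three categories fail. That is a minimum: the fracture examples in step 5 are not assessed by a head CT either, and a head CT is the scan named in the Discussion.

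**What does *these criteria* refer to?** There are two possible readings.

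1. *Broad*: every absolute contraindication in step 5. All three categories then conflict with step 3.
2. *Narrow*: only the bleeding-risk examples in the sentence immediately before. Step 3 would then govern the two history items within Selecting Change. Two problems remain. Medical conditions that promote bleeding are themselves among those examples, so they still go to a scan. And the Discussion lists a contraindication to anticoagulation and a high intracranial bleeding risk as alternatives joined by *or*, and sends both to a head CT and then into the protocol. That brings the history items back in.

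The conflict therefore survives on either reading, for one category within Selecting Change and for all three once the Discussion is read with it.

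**Stop rule.** Step 3 ends cPpx at discharge. Step 6 asks for two conditions, discharge and no longer being immobilized. They part only for a patient who leaves hospital still immobilized: step 3 stops and step 6 continues. The later Discussion sentence, "We do not provide a prescription for mechanical VTE prophylaxis other than early mobilization with physical therapy", concerns mechanical measures and does not decide the matter for cPpx.

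**Scale.** The documents give no share of patients with these histories. For orientation only, the NSQIP query year in the Introduction had 320 cases. An assumed 1% would be 320 × 0.01 = 3.2 patients a year, and an assumed 5% would be 320 × 0.05 = 16. Both shares are assumptions, and the 320 are all neurosurgery cases, not the elective group that step 3 governs.

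**The case against.** The strongest reply is that steps 3 and 5 refer to each other and are meant to be read together: withhold, scan, then include. For bleeding-type contraindications this is right, and no fault is found there. The reply also holds that the antecedent in step 5 is ambiguous and that the Discussion sentence is a summary, not the operative step. The ambiguity is real, but the narrow reading does not remove the conflict, for the reasons given in the working.

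It can also be said that Figure 1, the flowchart staff actually use, is not shown and may be clear. That is so, and what staff did at the bedside is unknown. The point concerns the printed steps. Outcomes also provides for case review of bleeding events and for adjusting the protocol, which limits the harm without making the rule consistent.

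Several stronger readings are tempting and are not supported:

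- *Step 5 admits every patient with an absolute contraindication.* Entry depends on the scan, and for bleeding that imaging can assess this is a reasonable gate.
- *Recent spine or brain surgery is a contraindication, so the protocol rules out its own population.* Step 5 states that item for trauma patients, whereas step 3 governs elective surgery.
- *The start times conflict.* Step 3 starts at 24 hours and the Discussion says "We have elected to initiate cPpx for all admitted patients on the neurosurgery service within 24-48 hours of scheduled surgery". These are compatible, given that step 2 places stability imaging at 24 to 48 hours.
- *Step 6 orders cPpx after discharge.* It speaks of therapy, no step provides for supply after discharge, and the project is about admitted patients. Only a wording mismatch remains.

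**Conclusion.** The point holds as a minor one. For at least three listed absolute contraindications, the printed rules give opposite instructions, and one of them could lead to an anticoagulant being given on a test that does not address the reason for withholding it. This rests on taking *inclusion* and *enter the protocol* to mean entry to the cPpx pathway, which is the natural sense in a list of treatment steps, and on the Discussion sentence being meant as it stands.

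The number of patients affected cannot be derived from the documents. A reader might infer that the primary comparison is biased because some patients drop out of it. The documents do not support that: the Methods Overview places all patients admitted for postoperative neurosurgical care under the protocol and takes the preceding 12 months of admissions as control. A reader might also want a figure for lost adherence. The article does not define how adherence is scored, so any percentage would only repeat an assumption. No estimand, test or stated number changes.

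**What to change.** 1. **Step 5 and the Discussion sentence.** Limit scan-then-start to hemorrhage or bleeding risk that imaging can assess: active or intracranial hemorrhage, TBI, SCI, and recent spine or intracranial surgery in trauma patients. Say that cPpx is held until the scan of the relevant site is stable.
2. **All other absolute contraindications**, including an earlier complication on anticoagulants, recurrent VTE on adequate cPpx, and medical conditions that promote bleeding. State: *no protocol cPpx and no entry by scan; documented individual clinical decision*.
3. **Step 3.** Make the cross-reference to step 5 carry the same distinction: held until a stable scan where imaging can assess the risk, otherwise withheld. Check that the flowchart agrees.
4. **Denominator.** State that these patients stay in the VTE rate in both periods, whether cPpx is given, held or withheld.
5. **Stop rule.** Use one wording in steps 3 and 6. Stopping at discharge fits the stated inpatient scope; if the clinical team intends longer cover, it should say so in both places.

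The cost is edits to steps 3, 5 and 6 and one Discussion sentence, a flowchart check and a short notice to trained staff. No new data are needed. If data collection has ended, the report should state which rule was in force.

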While the majority of VTEs are asymptomatic, symptomatic VTEs may result in serious adverse events or death [4]. Therefore, prophylaxis of VTE plays a major role in reducing adverse events and unexpected mortality in patients undergoing neurosurgery. An ACS NSQIP data query for Ochsner Department of Neurosurgery performed on August 1, 2022, for the period of July 1, 2020, to June 30, 2021, yielded incidence rates of VTE as follows: a total of 8 events per 320 total neurosurgery cases for a rate of 2.5%, whereas the predicted rate of VTE was calculated to be 2.83% and the expected rate based on the national average rate of VTE was calculated to be 3.27%. This has resulted in an OR calculation of 0.86 (95% CI 0.52-1.42). When stratified by the type of neurosurgery, the VTE incidence rate was 0.76%, where a VTE event occurred in 1 case out of a total of 132 spine neurosurgery cases. The predicted rate for spine neurosurgery was 1.78% and the expected rate for spine neurosurgery cases was 2.24%, with an OR of 0.77 (95% CI 0.37-1.61). The rate of VTE after neurosurgery for brain tumors at Ochsner was 3.52%, based on 5 cases out of 142 total brain tumor neurosurgery cases. The predicted rate of VTE incidence for patients undergoing neurosurgery for brain tumor was 3.45% and its expected rate was 3.42%, with an OR of VTE incidence among patients after brain tumor neurosurgery of 1.01 (95% CI 0.63-1.63).

Although the incidence of VTE at Ochsner Health Department of Neurosurgery is within the expected range of nationwide data [1-3], the lack of a department- or hospital-based protocol for postoperative VTE prophylaxis results in a heterogeneity of patient care and may contribute to unexpected outcomes. Current practice dictates that individual physicians apply their chosen set of VTE prophylaxis guidelines [17]. This further contributes to a heterogeneity of patient care since most guidelines provide inconsistent recommendations (Multimedia Appendix 1). This creates a gap in patient care that could potentially be bridged through a consistent set of department VTE prevention guidelines, which would aim to diminish patient care variability and reduce the incidence of VTE below the national average rates.

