## Methods

### Overview

This project is well aligned with the Institute of Medicine’s 6 domains of quality health care and was designed according to the Institute for Healthcare Improvement steps to a good QI project [22]. It aims to avoid harm to patients while being effective in providing prophylaxis according to a risk-based approach. Specifically, the adaptive design assessing outcomes and process measures and implementing incremental change on a quarterly basis ensure the safety of this QI project. Our protocol follows the Agency for Healthcare Research 2017 guidelines to ensure patient safety while implementing this protocol [23]. This quality improvement project has been designed and reported in accordance with the SQUIRE 2.0 (Standards for Quality Improvement Reporting Excellence) guidelines. SQUIRE is the most appropriate framework for reporting system-level interventions aimed at improving health care quality, safety, and outcomes. This manuscript addresses all relevant SQUIRE elements [24]. Further, this project is patient-centered and aims to ensure equitable care for patients by consistently including all eligible individuals in the protocol without discriminating based on demographics. Finally, it is a timely and efficient protocol, reducing inconsistent application of variable guidelines and thus potentially avoiding supplies and staff waste. The assessment of the impact of this protocol on VTE incidence is at 12 and 24 months post implementation, with interim analyses every 3 months to ensure continuous quality improvement. The goal is a 50% decrease in the overall VTE incidence in patients undergoing neurosurgery from 2.5% to 1.25%, with a greater decrease in incidence of VTE among patients undergoing neurosurgical procedures for malignant pathology (cranial or spine). Targeting a reduction to 1.25% represents an achievable improvement that aligns with outcomes seen in successful QI initiatives with standardized protocols [25-27]. For example, the Mercy Hospital Springfield Neurosurgery VTE quality improvement initiative found that VTE occurrence rates in neurosurgery decreased from 3.97% at the time of protocol initiation to 0.72% in January 2020 [26]. All patients admitted to the neurosurgery service for postoperative care will be managed according to the new protocol after the implementation date. The incidence of VTE among patients admitted during the previous 12 months will serve as a control.

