### Outcomes

The primary outcome measure is the rate of VTE. Benchmark data for the primary outcome is derived from ACS NSQIP VTE rates for Ochsner Neurosurgery and the nationwide ACS NSQIP VTE rate. Benchmarks are 2.5% for Ochsner Neurosurgery and 3.27% for the national incidence rate [3]. Secondary outcome measures include the rate of PE, the rate of symptomatic DVT, and the rate of PE-associated mortality.

Process measures have an impact on the primary and secondary outcomes and will include staffing at the time of VTE diagnosis, volume of patients per resident physician, and the percentage of patients at high risk. Balancing measures include the complexity of patients based on VTE risk and history of VTE despite prophylaxis, medication reconciliations, communication with other services, and volume of patients on the neurological ICU. Procedure and patient risk factors of VTE will be included in the analysis as confounding variables. Unintended consequences such as supratherapeutic anticoagulation or bleeding events, delays in mobilization or surgery due to protocol requirements, or variation in adherence will be monitored as well. The mentioned unintended consequences will be monitored through case review and clinical incident reports, and adjustments to the protocol will be made through the Plan-Do-Study-Act cycle framework.

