## Results

The desired timeframe for implementing the Neurosurgery VTE prophylaxis protocol is within 6 months of QI project approval, with 1 month of “adaptation time.” Adaptation time is defined as the time between training the staff involved in the project and starting the timeline for outcomes assessment. Department project approval occurred on February 16, 2023, and the project adaptation time began on August 1, 2023.

Data collection is scheduled for completion in 2024, with analysis expected by March 2025. We anticipate a 50% reduction in VTE incidence (from 2.5% to 1.25%) following implementation of a standardized department-wide cPpx protocol. The primary outcome is the incidence of VTE. To assess whether implementation of the protocol results in a meaningful improvement compared to the standard of care, we will use a pre-post design comparing outcomes in the 12 months before and 12 months after the protocol implementation. We will evaluate differences in VTE rates using chi-square or Fisher exact test to compare the proportion of VTE events pre-implementation versus post-implementation. The justification for the chi-square test is that it is appropriate for large samples with expected counts ≥5. The Fisher exact test will be used as a backup for smaller subgroup comparisons where expected frequencies are low. In order to mitigate confounding, we will use multivariable logistic regression, using VTE occurrence as the dependent variable, with covariates including patient-level and procedural risk factors such as BMI, malignancy, surgery type (cranial vs spine), and immobility. The justification is that regression modeling will help isolate any independent effects of the protocol on VTE rates. To account for continuous secondary outcomes, we will perform stratified subgroup analyses for patients with malignancy, those undergoing cranial versus spine procedures, and those receiving LMWH versus UFH. The justification for this is that we will protect against or identify subgroups that experience differential VTE risk. A stratified analysis will determine if the protocol is equally effective across populations.

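### The primary VTE comparison is specified twice, with different tests, comparators and time points, and nothing says which governs

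*Protocol article*

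**What the plan says.** The protocol article describes the analysis of the primary outcome, the VTE rate, in several places.

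- **Methods, Selecting Change:** the formal analysis is to use Student's method, as a "test comparing NSQIP and postprotocol end-of-study VTE rates at both 12 and 24 months post implementation". It does not say whether this t test is one-sample or two-sample, or which NSQIP rate is meant.
- **Methods, Outcomes:** two NSQIP rates are given. "Benchmarks are 2.5% for Ochsner Neurosurgery and 3.27% for the national incidence rate".
- **Methods, Overview:** "The incidence of VTE among patients admitted during the previous 12 months will serve as a control". The same section places the assessment at 12 and 24 months.
- **Results:** a "pre-post design comparing outcomes in the 12 months before and 12 months after the protocol implementation", with the test given as follows: "We will evaluate differences in VTE rates using chi-square or Fisher exact test to compare the proportion of VTE events pre-implementation versus post-implementation". Chi-square is for expected counts of at least 5, with Fisher as the backup. No 24-month comparison appears here.
- **Introduction, Overview:** the local 2.5% is 8 events in 320 cases "for the period of July 1, 2020, to June 30, 2021".
- **Results, closing paragraph:** success is a reduction of at least 50% from baseline, written as 2.5% to 1.25% or less.

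**The concern.** One primary question has two incompatible answers on the page, and neither is called primary, secondary or sensitivity. With both in force, the test, comparator and time point could be settled after the data are seen.

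The comparators are also different patients. Adaptation time began on August 1, 2023, so the previous 12 months run from about August 2022 or slightly later. The local NSQIP window closed in June 2021, more than a year before that control period opens. A test against NSQIP and a test against the previous 12 months are therefore two different comparisons.

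If the NSQIP rate is treated as a fixed value, the sampling error of an 8-event baseline is ignored. A one-sample t test makes this worse, because it estimates its standard error from the handful of post-period events.

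**Working it through.** **Inputs from the protocol article.** Local NSQIP count 8/320 (Introduction, Overview); national rate 3.27% (Outcomes); target 1.25% (Methods, Overview; Results).

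**Assumptions, because the article gives no figure.** 320 post-period cases, as in the NSQIP sample; two-sided 0.05; 8/320 as a stand-in for the unknown pre-period count.

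**Step 1. Reproduce the stated figures.** 8/320 = 0.0250, and half of that is 0.0125, which is 4/320. Both agree with the article.

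**Step 2. Results specification: chi-square, 8/320 against 4/320.** Pooled proportion = 12/640 = 0.01875. Standard error = √(0.01875 × 0.98125 × 2/320) = 0.01072. z = 0.0125/0.01072 = 1.166, so chi-square = 1.36 and p = 0.244. The smallest expected count is 6.0, so chi-square is the applicable test under the article's own rule (Fisher would give 0.383).

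**Step 3. Selecting Change specification, read as a two-sample t test.** On the individual 0/1 data, 8/320 against 4/320 gives t = 1.165 and p = 0.244. The change of test alone makes no practical difference.

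**Step 4. Selecting Change specification, read as a one-sample t test.** Standard error = √(0.0125 × 0.9875/319) = 0.00622.

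- Against 2.5%: t = (0.0125 − 0.025)/0.00622 = −2.01, p = 0.045. The exact binomial test gives 0.206.
- Against 3.27%: t = (0.0125 − 0.0327)/0.00622 = −3.25, p = 0.0013. The exact binomial test gives 0.0395.

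**Step 5. Vary the period size.** Equal periods, with a pre-period rate near 2.5% and a post-period rate near 1.25%:

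| Cases per period | Events pre / post | Chi-square p | One-sample t against 2.5%, p |
|---|---|---|---|
| 320 | 8 / 4 | 0.244 | 0.045 |
| 500 | 12 / 6 | 0.154 | 0.008 |
| 640 | 16 / 8 | 0.099 | 0.005 |
| 800 | 20 / 10 | 0.065 | 0.0015 |
| 1000 | 25 / 12 | 0.031 | 0.0002 |

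**Step 6. False-positive rate of the one-sample t test.** At n = 320 against 2.5%, 4 events give p = 0.045 and 5 events give p = 0.178, so a decrease is declared at 4 or fewer events. If the true rate stays at 2.5%, P(X ≤ 4 | 320, 0.025) = 0.097, against a nominal 0.025 on that side. The t statistic is undefined at zero events; counting that case as a decrease adds only 0.0003.

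**Step 7. Precision of the baseline.** The exact 95% confidence interval for 8/320 is 1.1% to 4.9%, so 2.5% is far from a known constant and the interval includes the 1.25% target.

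**The case against.** The strongest reply has four parts.

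1. **The reversal needs a one-sample reading that the article never states.** This stands. A reader might infer that choosing the t test over chi-square is what changes the answer, but the two-sample t test gives the same 0.244. Nor does fixing the baseline at 2.5% produce significance by itself: the exact binomial gives 0.206. Only the one-sample t test against 2.5% crosses 0.05.

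2. **No section names 3.27% as the value tested.** This also stands. A reader might infer that the plan would credit the protocol with beating the national rate. However, the goal is written throughout as 2.5% to 1.25%, which makes the local rate the natural NSQIP comparator. The article also reports an odds ratio of 0.86 (95% CI 0.52 to 1.42), so no prior advantage over expectation was established. What remains is that the bare reference to NSQIP leaves the choice open.

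3. **The split in significance depends on period size.** It does: it is gone by about 1000 cases per period, and the article gives no post-period size.

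4. **Success is a point-estimate rule, and the Results section is the fuller, justified specification.** This lessens the harm but does not remove it. Nothing says the Results text governs, and Selecting Change calls its own test the formal analysis. The success rule also uses 2.5% as baseline, so it carries the same ambiguity about comparator.

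**Conclusion.** The plan is wrong as written: two specifications of the primary comparison disagree on test, comparator and time point, and no section ranks them. This rests on the text alone and needs no assumption.

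The numerical consequence is conditional. With 320 post-period cases, two-sided 0.05 and 8/320 as the stand-in pre-period, a result exactly on target is not significant by chi-square or by a two-sample t test. It is significant by a one-sample t test against either NSQIP rate. On the one-sample reading against 2.5%, an unchanged true rate would be declared a decrease 9.7% of the time. The documents do not support the broader claim that following one section rather than the other always reverses the result. It can do so, under a reading that the article leaves open and at period sizes up to about 800.

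**What to change.** - **Selecting Change:** replace the t test with the Results analysis as the single primary analysis. Compare the post-period with the 12 months immediately before implementation, with stated calendar windows and the same data source and VTE definition in both periods. Use chi-square, or Fisher if any expected count is below 5, and report the risk difference and risk ratio with 95% confidence intervals.
- **Time point:** make 12 months primary and label any 24-month analysis secondary. The Abstract has data collection ending by December 2024, less than 24 months after August 2023, so the 24-month point needs reconciling with the timeline in any case.
- **Success rule in Results:** measure the 50% reduction against the observed pre-period rate and keep 2.5% as the planning value.
- **NSQIP:** label comparisons with the 2020-21 local rate and the 3.27% national rate as secondary or descriptive, naming the rate used.

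The cost is a change of wording plus the pre-period count, which the Methods Overview and Results already require. The downside is small: a result at target will probably look less favourable, and at about 320 cases per period it would not be significant.
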